## **8.2 Randomisation, blinding and treatment allocation**

The website randomization tool provided by REDCap will be used. A block randomization will be used with an allocation ratio of 1:1. The randomization chart, including block size, will be established by an independent data manager before the start of the study. Consequently, treatment allocation sequence will be concealed for patients, care providers and researchers (including outcome assessors). The outcome assessors in this study are patients (self-assessment using questionnaires) and care providers (Clavien Dindo classification, CTCAE, recurrence and survival).

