Dietetic consultations will be scheduled biweekly. Depending on the patients' needs and preferences, the frequency of consultations may be increased, e.g., in case of weight loss or inability to use oral intake. These consultations may take place in-person at the outpatient department or through video or telephone calls. The first consultation takes on average 30 minutes, follow-up consultations on average 15 minutes. We expect that in 10-20% of included patients dietary advice in the form of an energy and protein enriched diet will be sufficient and 80-90% of patients will be offered oral nutritional supplements to meet estimated nutritional requirements. Patients rarely need enteral nutritional support in this prehabilitation stage.

Nutritional prehabilitation will start as soon as patients are included in the study, which is within one week after their first visit to the outpatient department, depending on the time needed to consider participation in the trial. The expected variation in duration of the intervention is three to four-and-a-half weeks. The **prehabilitation** intervention ends as

soon as treatment for their head and neck cancer commences. Patients will still be receiving nutritional care as is standard care (i.e., postoperatively and/or during (chemo)radiotherapy). Nutritional care given during treatment is the same as nutritional care that is outlined in this paragraph (i.e., given as a prehabilitation intervention). Patients undergoing (chemo)radiotherapy are all counseled by a dietitian during their treatment. Patients undergoing surgery will receive nutritional care as indicated by their MUST score or as indicated by the “Perioperatief voedingsbeleid” guideline: inability to start oral intake within 48 hours after surgery or no more than 50% of the recommended daily energy intake on the fifth day postoperatively [21].

Patients enrolled in the control arm of the study will receive standard care, which means they will not receive any nutritional counseling or nutritional intervention before treatment commences.

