## 8. METHODS

### 8.1 Study parameters/endpoints

#### 8.1.1 Main study parameter/endpoint

The primary outcome will be adverse events (intra- and postoperative complications and (chemo)radiotherapy toxicity). Relevant complications include hemorrhage, infection and wound healing disorders including dehiscence and fistula.

Complications will be measured within 30 days after surgery using the Clavien-Dindo classification and evaluated during hospital stay and planned and unplanned outpatient visits [22]. Clavien-Dindo grade  $\geq 2$  complications will be deemed clinically relevant. Toxicity will be evaluated using the Common Terminology Criteria for Adverse Events (CTCAE), version 4.0, at 6 and 12 weeks after the start of (chemo)radiotherapy [23]. The following domains are scored within the CTCAE: xerostomia, taste, throat pain, oral pain, general pain, dysphagia, hoarseness and mucositis. Clinically relevant toxicity will be defined as CTCAE toxicity grade  $\geq 3$ , irrespective of the mentioned domains.

Both complications and (chemo)radiotherapy toxicity are evaluated as part of our current standard practice.

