### 10.1 Primary study parameter(s)

The primary outcome will be adverse events (intra- and postoperative complications and (chemo)radiotherapy toxicity). Relevant complications include hemorrhage, infection and wound healing disorders including dehiscence and fistula. Complications will be measured within 30 days after surgery using the Clavien-Dindo classification and evaluated during hospital stay and planned and unplanned outpatient visits [22]. Clavien-Dindo grade  $\geq 2$  complications will be deemed clinically relevant. Toxicity will be evaluated using the Common Terminology Criteria for Adverse Events (CTCAE), version

4.0, 6 and 12 weeks after the start of (chemo)radiotherapy. The following domains are scored within the CTCAE: xerostomia, taste, throat pain, oral pain, general pain, dysphagia, hoarseness and mucositis. Clinically relevant toxicity will be defined as CTCAE toxicity grade  $\geq 3$ , irrespective of the mentioned domains.

For analysis of between-group differences in the primary outcome, a logistic regression analysis will be performed. The endpoints complications and toxicity will be dichotomized. In case of unbalance between the intervention and the control group, adjusted logistic regression analyses will be performed. A  $p$ -value  $< 0.05$  will be considered as statistically significant.

Subgroup analyses will be performed using the following variables:

- (intended) type of treatment (surgery versus (chemo)therapy)
- Subsite (larynx versus hypopharynx versus oropharynx versus oral cavity)
- Skeletal muscle mass (LSMI in  $\text{cm}^2/\text{m}^2$ )
- Duration of nutritional prehabilitation intervention
- Number of dietetic consultations
- Dietary intake using 24-hour recall

These variables will be added to the regression analyses

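### Treatment modality determines the endpoint instrument and much of the background dietetic care, yet randomisation is unstratified and the primary model adjusts only if imbalance is seen

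*Protocol*

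**What the plan says.** **Allocation.** Section 8.2: "A block randomization will be used with an allocation ratio of 1:1". It adds that "The randomization chart, including block size, will be established by an independent data manager before the start of the study". No stratification factor is named there or elsewhere in the protocol.

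**Background care.** Section 5.1: "Patients undergoing (chemo)radiotherapy are all counseled by a dietitian during their treatment". For the other modality, "Patients undergoing surgery will receive nutritional care as indicated by their MUST score", or when a perioperative guideline criterion is met. The same section foresees both modalities in one patient, since standard nutritional care is given "postoperatively and/or during (chemo)radiotherapy".

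**Endpoint.** Section 8.1.1: "Complications will be measured within 30 days after surgery using the Clavien-Dindo classification", with grade 2 or higher counting as relevant. Toxicity is scored on CTCAE "at 6 and 12 weeks after the start of (chemo)radiotherapy", with grade 3 or higher in any of eight domains counting.

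**Analysis.** Section 10.1 plans a logistic regression on the dichotomised endpoint, with adjusted versions if the arms are unbalanced. It names neither the criterion for imbalance nor the covariates. The first subgroup variable, to be added to the regression, is "intended) type of treatment (surgery versus (chemo)therapy". Section 8.1.3 lists intended type of treatment among the baseline characteristics.

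**The concern.** In most trials an unstratified list is a matter of taste. Here modality does more than predict outcome. A surgical patient and a (chemo)radiotherapy patient are judged on different scales, with different grade thresholds and at different times, so equal event rates in the two groups would be a coincidence. The background also differs. Every control patient on (chemo)radiotherapy sees a dietitian during treatment, and section 5.1 says this care is the same as the prehabilitation care. A surgical control gets it only on indication.

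The protocol treats modality as important enough to be its first subgroup variable, but neither balances it nor commits to having it in the primary model. Two things are at stake: avoidable chance variation in a trial of 128, and a primary analysis whose form depends on a look at the data with no stated trigger. A smaller matter is that the two-level split does not say where a patient planned for surgery plus (chemo)radiotherapy belongs.

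**Working it through.** **Inputs from the protocol (section 4.4).** Total 128, so 128/2 = 64 per arm; event rates 15% and 40%; planned difference 25 points. The protocol gives no figure for modality imbalance, so there is none to reproduce.

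**Assumptions, not in the protocol.** Share of one modality: 50%, with 20% to 40% as alternatives. Gap in event rate between modalities: 20 to 30 points. Block size 4 in the simulations.

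**1. Spread of the imbalance.** SD of the between-arm difference in share = sqrt(2 × p × (1 − p)/64).
- p = 0.5: sqrt(2 × 0.5 × 0.5/64) = 0.088, or 8.8 points; 1.96 × 8.8 = 17 points.
- Simulating 128 patients in unstratified blocks of 4 gives SDs of 7.1 to 8.9 points for shares of 20% to 50%.

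**2. Probability and resulting shift.** Exact probabilities use two independent binomials of size 64. Shift in the arm difference = (imbalance in share) × (event-rate gap).

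| Imbalance | As share | Probability, p = 0.5 | Probability, p = 0.3 | Shift at 20-point gap | Shift at 30-point gap |
|---|---|---|---|---|---|
| 7 or more patients | 7/64 = 10.9 points | 25% | 21% | 2.2 points | 3.3 points |
| 11 or more patients | 11/64 = 17.2 points | 6% | 4% | 3.4 points | 5.2 points |

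The shifts are those at the lower edge of each row. Against the planned 25 points, the first row is 2.2/25 = 9% to 3.3/25 = 13%.

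**3. Comparison with sampling error.** The standard error of the arm difference at the planned rates is sqrt(0.15 × 0.85/64 + 0.40 × 0.60/64) = 0.076, or 7.6 points. A shift of 2.2 to 3.3 points is therefore 0.3 to 0.4 of a standard error.

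**4. Error rates by simulation.** Surgical share 40% (assumed), odds ratio as implied by 15% versus 40%, unstratified blocks of 4, unadjusted two-proportion test against a modality-stratified Cochran-Mantel-Haenszel test.

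| Control rate, surgery / radiotherapy | Type I error, unadjusted | Power, unadjusted | Power, adjusted |
|---|---|---|---|
| 40% / 40% | 0.054 | 90.0% | 89.5% |
| 25% / 50% | 0.050 | 88.1% | 88.9% |
| 55% / 30% | 0.054 | 87.5% | 88.9% |
| 10% / 60% | 0.055 | 79.2% | 85.8% |

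The unadjusted test keeps its level throughout. Adjustment gains about one point of power in the moderate cases and nearly seven in the extreme one. These runs compare two fixed analyses; they do not model a choice between them made after inspecting balance.

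**5. Stratifying without adjusting.** With stratified blocks of 4 the arms differ by at most 2 patients per stratum, 2/64 = about 3 points. In the extreme case, however, the unadjusted test then becomes conservative (type I error 0.025), while the adjusted test stays at 0.049. The covariate in the model matters more than the stratified list.

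**The case against.** **The protocol already has a remedy.** Section 10.1 provides adjusted regression if the arms are unbalanced and says that type of treatment will be added to the regression. This is a real mitigation. What it leaves open is the trigger and the covariates, so the primary model is still settled after the data are seen. Modality enters with certainty only as a subgroup variable.

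**Chance imbalance is not bias.** This stands. It is already part of the standard error, and the simulations show no inflation. A reader might infer that an unstratified list threatens validity; the calculations do not support that.

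**The larger shift is unlikely.** A reader might put the 25% probability beside a shift of 3.4 to 5.2 points. They do not belong together: the larger shift needs about 11 patients, which has a probability of about 6%.

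**Subgroup by treatment received.** The bracketed word for intention in section 10.1 might suggest that patients could be classified by treatment actually given, after open-label allocation. Section 8.1.3 lists intended treatment as a baseline characteristic, and nothing says patients are reclassified later. This is loose wording, not a rule.

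**Combined treatment.** It would be too strong to say that such patients cannot fit the two-level split. They could be placed under surgery, for example. The protocol does not say which, and that is all that remains. The evidence that both modalities occur in one patient is in section 5.1. The list of specialists in section 8.6 concerns follow-up after withdrawal and adds little.

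**Feasibility.** Section 3 randomises patients as soon as they are enrolled, and section 5.1 starts the intervention within a week of the first visit. The protocol does not say when the treatment plan is settled. If that comes later, waiting for it would shorten prehabilitation. This limits the advice to stratify.

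**Conclusion.** The point holds as a worthwhile improvement in design and prespecification, not as an error that invalidates the trial. Modality determines the endpoint instrument and much of the background dietetic care, yet it is neither balanced by design nor fixed in the primary model.

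At an assumed 50% share, an imbalance of 7 or more patients has a probability of about 25% and shifts the arm difference by about 2 to 3 points under an assumed 20- to 30-point rate gap. That is well inside the 7.6-point standard error. The gain in power from adjustment is about one point under moderate assumptions and becomes material only with very different event rates by modality. Both the share and the gap are assumptions, because the protocol gives neither.

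The stronger part of the case is the model choice. An imbalance-triggered adjustment with no stated criterion or covariates lets the primary analysis depend on the data, and avoiding this costs almost nothing.

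**What to change.** 1. **Section 10.1, primary model.** Replace the imbalance-triggered adjustment with a logistic model that always contains intended treatment modality as recorded at baseline.
2. **Section 10.1, classification.** State that patients are classified by the treatment intended at randomisation, and name the category for those planned for surgery plus (chemo)radiotherapy, either as a third level or as an explicit part of one of the two. Use the same variable for the subgroup analysis.
3. **Section 8.2, if feasible.** Where the treatment plan is known at enrolment and recruitment allows, stratify the REDCap block list by this variable. Do this only together with step 1, since stratifying without adjusting can make the test conservative.

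**Cost.** The sample size does not change, and the variable is already to be collected. Steps 1 and 2 are wording changes and remain possible after recruitment has begun, provided they are settled before outcome data are examined. Step 3 needs separate block lists and entry of the intended plan before randomisation. Patients whose treatment later changes keep their stratum. If the plan is often not settled at enrolment, step 3 should be dropped rather than delay the start of prehabilitation.

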## **8.3 Study procedures**

*Procedures that are part of standard clinical practice:*

- Diagnostic head and neck CT scans, which will be used to measure pre-treatment CSMA at the level of C3 [29, 30, 32]. The acquired CSMA at the level of C3 will be converted to CSMA at the level of L3 and subsequently corrected for patients' squared height to obtain the LSMI. Low LSMI will be defined as lower than 46.5 cm^2/m^2 for men and lower than 37.9 cm^2/m^2 for women [13];
- Intra- and postoperative complications measured within 30 days after surgery using the Clavien-Dindo classification;

- (Chemo)radiotherapy toxicity measured 6 and 12 weeks after the start of (chemo)radiotherapy using the CTCAE version 4.0;
- EORTC H&N35 measured for two years at baseline and at 3, 6, 12, 18 and 24 months;
- EORTC C30 measured for two years at baseline and at 3, 6, 12, 18 and 24 months;
- EQ-5D-5L measured at baseline and at 3, 6, 12, 18 and 24 months.

*Procedures that are not part of standard clinical practice and all of which will not postpone diagnostic procedures or treatment:*

- Grip strength, which will be measured using a Jamar hydraulic handheld dynamometer as recommended by the American Society of Hand Therapists and expressed in kilograms. Patients will be asked to squeeze maximally with each hand. Each hand will be measured three times. Low grip strength will be defined as lower than 27 kg in men and lower than 16 kg in women [25]. This measurement will be performed at baseline and takes less than five minutes to complete;
- BIA-measurements to estimate body composition, including body fat and muscle mass, using a weak electric current that flows through the body. The measurement will be performed at baseline, just before the treatment starts, and three months after the final treatment. It takes on average 15 minutes to complete;
- EAT-10 in the first two years of follow-up at baseline and at 3, 6, 12, 18 and 24 months after last treatment. The EAT-10 consists of 10 questions in three domains: functional, emotional and physical. Time to complete the EAT-10 is on average two minutes;
- iMCQ in the first year of follow-up at baseline and at 3, 6 and 12 months after last treatment. The iMCQ consists of 20 questions. Time to complete the iMCQ is on average 10 minutes;
- iPCQ in the first year of follow-up at baseline and at 3, 6 and 12 months after last treatment. The iPCQ consists of 18 questions, of which nine are general questions to collect demographic information, such as age, sex and work status. Productivity losses are measured in three separate modules (absenteeism, presenteeism and productivity losses of unpaid work). Time to complete the iPCQ is on average 5 minutes.

#### **8.4 Withdrawal of individual subjects**

Subjects can leave the study at any time for any reason if they wish to do so without any consequences. The investigator can decide to withdraw a subject from the study for urgent medical reasons.

##### **8.4.1 Specific criteria for withdrawal (if applicable)**

Not applicable.

#### **8.5 Replacement of individual subjects after withdrawal**

To anticipate withdrawal of 5% of subjects, three more subjects than needed will be recruited per group. In case of withdrawal before randomization, the subject will be replaced for a new subject. If more than 5% of subjects withdraw before completing the intervention (i.e., nutritional prehabilitation) or before completing the primary endpoint (intra- and postoperative complications within 30 days after surgery or toxicity six weeks after the start of (chemo)radiotherapy), they will be replaced with additional subjects to ensure a total of 128 subjects for the evaluation of the primary endpoint.

#### **8.6 Follow-up of subjects withdrawn from treatment**

Subjects withdrawn from treatment will continue to receive the standard medical treatment and five-year follow-up provided by their head and neck surgeon and/or radiotherapist and/or medical oncologist. They will no longer have to complete the questionnaires that are part of this study.

#### **8.7 Premature termination of the study**

Reasons for premature termination of the study may be:

- If the positive decision of the METC is irrevocably revoked;
- If a reasonable case can be made for terminating the study in the interests of the health of the subjects:
  - o If continuation of the study does not serve any scientific purpose and this is confirmed by the METC that has issued a positive decision on the study;
  - o If the subsidising party has been declared insolvent;
  - o If either the sponsor or the subsidising party is dissolved as a legal entity;

- If the project leader is no longer capable of performing the tasks of project leader and no replacement agreeable to all parties can be found;
- If circumstances beyond the control of the sponsor, investigator or subsidising party make it unreasonable to continue the study.

## **9. SAFETY REPORTING**

### **9.1 Temporary halt for reasons of subject safety**

In accordance with section 10, subsection 4, of the WMO, the sponsor will suspend the study if there is sufficient ground that continuation of the study will jeopardise subject health or safety. The sponsor will notify the accredited METC without undue delay of a temporary halt including the reason for such an action. The study will be suspended pending a further positive decision by the accredited METC. The investigator will take care that all subjects are kept informed.

### **9.2 AEs, SAEs and SUSARs**

#### **9.2.1 Adverse events (AEs)**

Adverse events are defined as any undesirable experience occurring to a subject during the study, whether or not considered related to the experimental intervention (i.e., nutritional prehabilitation). All adverse events reported spontaneously by the subject or observed by the investigator or his staff will be recorded up until 6 weeks after last treatment, thereafter only SAEs will be recorded.

Any event involving adverse drug reactions, illnesses with onset during the study or exacerbations of pre-existing illnesses will be recorded, including but not limited to clinically significant changes in physical examination findings and abnormal objective test findings (e.g., x-ray, ECG). The criteria for determining whether an abnormal objective test finding should be reported as an AE are as follows:

- The test result is associated with clinically significant symptoms, and/or;
- The test result leads to a discontinuation from the clinical trial, significant additional concomitant drug treatment or other therapy and/or;
- The test result leads to any of the outcomes included in the definition of a SAE, and/or;
- The test result is considered to be clinically relevant by the investigator.

#### **9.2.2 Serious adverse events (SAEs)**

A serious adverse event is any untoward medical occurrence or effect that:

- results in death;
- is life threatening (at the time of the event);
- requires hospitalisation or prolongation of existing inpatients' hospitalisation;
- results in persistent or significant disability or incapacity;

- is a congenital anomaly or birth defect; or
- any other important medical event that did not result in any of the outcomes listed above due to medical or surgical intervention but could have been based upon appropriate judgement by the investigator.

An elective hospital admission will not be considered as a serious adverse event.

The investigator will report all SAEs to the sponsor without undue delay after obtaining knowledge of the events, except for the following SAEs:

- (prolonged) hospitalisation or intervention due to: postoperative hemorrhage, infection and wound healing disorders, which all can be expected with standard of care (i.e., (major) head and/or neck surgery).
- hospitalisation or intervention due to: (chemo)radiotherapy toxicity such as vomiting, throat pain, oral pain, dysphagia, mucositis and blood value imbalances, which all can be expected with standard of care (i.e., 70 Gy (chemo)radiotherapy).

The sponsor will report the SAEs through the web portal *ToetsingOnline* to the accredited METC that approved the protocol, within 7 days of first knowledge for SAEs that result in death or are life threatening followed by a period of maximum of 8 days to complete the initial preliminary report. All other SAEs will be reported within a period of maximum 15 days after the sponsor has first knowledge of the serious adverse events.

#### **9.2.3 Suspected unexpected serious adverse reactions (SUSARs)**

Not applicable.

### **9.3 Annual safety report**

Not applicable.

### **9.4 Follow-up of adverse events**

All AEs will be followed until they have abated, or until a stable situation has been reached. Depending on the event, follow up may require additional tests or medical procedures as indicated, and/or referral to the general physician or a medical specialist. SAEs need to be reported till end of study within the Netherlands, as defined in the protocol.

